## Abstract

**Background:**

A comprehensive in-hospital patient management with reasonable and economic resource allocation is arguably the major challenge of health-care systems worldwide, especially in elderly, frail, and polymorbid patients. The need for patient management tools to improve the transition process and allocation of health care resources in routine clinical care particularly for the inpatient setting is obvious. To address these issues, a large prospective trial is warranted.

**Methods:**

The “Integrative Hospital Treatment in Older patients to benchmark and improve Outcome and Length of stay” (In-HospiTOOL) study is an investigator-initiated, multicenter effectiveness trial to compare the effects of a novel in-hospital management tool on length of hospital stay, readmission rate, quality of care, and other clinical outcomes using a time-series model. The study aims to include approximately 35`000 polymorbid medical patients over an 18-month period, divided in an observation, implementation, and intervention phase. Detailed data on treatment and outcome of polymorbid medical patients during the in-hospital stay and after 30 days will be gathered to investigate differences in resource use, inter-professional collaborations and to establish representative benchmarking data to promote measurement and display of quality of care data across seven Swiss hospitals. The trial will inform whether the “In-HospiTOOL” optimizes inter-professional collaboration and thereby reduces length of hospital stay without harming subjective and objective patient-oriented outcome markers.

**Discussion:**

Many of the current quality-mirroring tools do not reflect the real need and use of resources, especially in polymorbid and elderly patients. In addition, a validated tool for optimization of patient transition and discharge processes is still missing. The proposed multicenter effectiveness trial has potential to improve interprofessional collaboration and optimizes resource allocation from hospital admission to discharge. The results will enable inter-hospital comparison of transition processes and accomplish a benchmarking for inpatient care quality.

**Electronic supplementary material:**

The online version of this article (10.1186/s12913-019-4045-x) contains supplementary material, which is available to authorized users.

## Background

One of the major challenges of health-care systems, governments, and societies worldwide is a comprehensive in-hospital patient management with reasonable and economic resource allocation [1], especially in frail, polymorbid, and elderly patients. A lower level of education and a cognitive impairment are additional risk factors. [2]. Novel and optimized diagnostic and therapeutic approaches have increased expectation of life, resulting in increased polymorbidity and complexity. Moreover, elderly patients with high demands for medical, but also nursing and social care call for a tighter allocation of our health care resources [3, 4]. Whereas emergency hospitalizations are facilitated by chronic disease burden, co-morbidities, and frailty, the trigger for hospital admission is often a per se minor acute event (e.g. urinary tract infection), disrupting the fragile bio-psycho-social homeostasis of polymorbidity. In many cases, a post-acute transfer to a nursing care facility is required. The need for patient management tools to improve the transition process and allocation of health care resources in routine clinical care particularly for the inpatient setting is obvious.

### Challenges and current evidence

Misutilization and suboptimal resource allocation challenges safe and efficient, patient-centered in-hospital transition from the emergency department (ED) to a medical ward, and transition to home or post-acute care facilities [5]. Errors that lead to unplanned readmissions and preventable deaths are more common in polymorbid patients [6]. Since the majority of medical inpatients with chronic illnesses become hospitalized via ED (non-electively), optimized resource use must start at the ED with an improved triage.

The optimal organization of routine medical ward care in mostly polymorbid, elderly medical patients received less alertness than the handling of specific diseases. Specifically, there is a lack of large trials focusing on polymorbid patients and their objective outcomes [7]. The inter-professional team care approach with a comprehensive geriatric in-hospital assessment has been found effective to increase patients’ likelihood of being alive and living in their own homes after an emergency admission to hospital [8]. Conversely, many earlier studies were unable to link interdisciplinary team care interventions to affect existing metrics, partly because of limited methodology and outcome measures [9]. As recently shown in a review article, several innovative interprofessional and interdisciplinary healthcare interventions on medical wards usually have chosen length of hospital stay, mortality rates, readmission, or functionality as their primary outcome measures [10]. However, most interventions have not shown any effect on these patient-oriented outcomes and are therefore debatable and inconsistent. Few evidence suggests that an improved interprofessional collaboration would reduce adverse effects of care. Thus, a significant reduction in length of hospital stay have been reported due to contemporaneous secular reasons [11], which most of the published interventions did not reduce additionally. The majority of inpatient setting interventions were unlikely to reduce readmissions, neither to reduce mortality rates, nor to diminish need for nursing facilities after discharge. However, generalizability of these findings remains weak due to discrepancies between different healthcare systems and heterogeneous (inter-)national standards of care.

Recently, innovative strategies to synergize the concepts of implementation science, precision medicine, and learning health care systems have been advocated [12]. Using this experience, we will integrate evidence-based strategies (e.g., training, supervision, quality monitoring tools, system change interventions) into real-world practice [13].

### Rationale of the study and overall aim

The main reason for the large controversy of the different tool’s effectiveness in elderly, polymorbid patients is mainly explained by the current lack of evidence. Hence, a large prospective multicenter trial is warranted to investigate the effects of a patient in-hospital management tool (“In-HospiTOOL”). Using an interrupted time series (ITS) model to gather detailed treatment and outcome data of elderly, polymorbid medical patients during the in-hospital stay and 30 days after admission, we will investigate differences in resource use (Module 1), interprofessional collaborations (Module 2), and establish a representative benchmarking database to promote measurement and display of quality of care [14] across different sized Swiss hospitals (Module 3).

## Methods/design

### Aim and study design

The “In-HospiTOOL” study is a quasi-experimental investigator-initiated, multicenter effectiveness trial investigating the effects of a new patient in-hospital management tool to improve length of hospital stay and other outcomes using an ITS model. The overall 18-month study time is divided in a 6-month observational phase, a 6-month implementation phase, and a 6-month intervention phase.

### Setting, study sites and characteristics of participants

The multicenter trial includes seven secondary and tertiary care hospitals within Northern Switzerland. This allows to collect representative nation-wide patient-oriented data from polymorbid patients. All senior executive leaders have reassured full support for an optimal implementation of the “In-HospiTOOL” in their hospitals. Upon hospital admission, consecutive adult (age ≥ 18 years), polymorbid (> 1 diagnose) medical inpatients will be included in our study. Except for non-medical and non-adult patients there will be no exclusion criteria.

### Patient population

#### Intervention population

To reflect “daily practice”, we include consecutive adult medical inpatients independent of their diagnosis during the observation, implementation, and intervention period, respectively, into the analysis - like an intention-to-treat approach.

#### Control population

For our statistical approach as outlined below, we request data from the Federal Statistical Office to provide a nationwide comparability. We will use data on length of hospital stay. Age, gender, health care insurance, place of residence, main diagnosis, comorbidities, and study center will be used for statistical adjustment.

### Data collection process

The study period is divided into three 6-month phases, whereas the observation and the intervention phase until the end of January 2019 are season-matched, interrupted by a run-in non-season-matched implementation phase. The period of “In-HospiTOOL” implementation in the participating hospitals will be devoted to technical implementation, training of involved study personnel, nurses, social workers, physicians, and pilot testing. We will collect data throughout all three study periods by using electronic medical records and will contact all patients 30 days after hospital admission by phone interview. Data from the structured phone interviews will be stored on a data base using the secuTrial© software (secuTrial®; interActive Systems GmbH, Berlin, Germany).

### Theoretical aspects, hypothesis

#### Module 1 resource (mis-)utilization & allocation

We hypothesize that implementing the “In-HospiTOOL” in a nationwide multicenter setting will significantly shorten length of hospital stay without compromising patient outcomes and functional independence. Systematic early determination of clinical stability, estimation of the post-acute care referral probability (using the Post-acute care discharge [PACD] score [15]), fixing a possible discharge date after initial ED assessment as well as a tight interprofessional collaboration enabled through an electronical communication platform (“Visitentool”, Fig. 1) will result in decreased waiting times contributing to the shortening of length of hospital stay [16–18].

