#### Module 2 Interprofessional collaboration, integral hospital and post-acute patient transition

Transparent and systematic interprofessional communication will reveal factors for delay in these polymorbid patients (pending diagnostics, medical treatments, administrative and organizational elements) throughout the hospital stay. Doing so, we will identify regional and socioeconomic (e.g., health care insurance status) differences in the patient care continuum. We hypothesize that longitudinal observation of patient transition will further allow measurement of effective time from initial request to a post-acute care institution to effective transfer with corresponding internal and external delaying factors (Fig. 2). We will systematically examine patient satisfaction, hypothesizing that it will not decrease upon the study intervention. Implementing a reengineered discharge questionnaire including the teach-back methodology, we aim to improve patient education [19, 20]. This effort will not only strengthen interprofessional coordination and communication, but also increase health care continuity across all hospital transition steps. Moreover, we systematically investigate reasons for low satisfaction.

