### Endpoints

All patients will be daily assessed during hospitalization and contacted 30 days after admission by phone for a structured and blinded interview to assess primary and secondary endpoints.

The primary endpoint of this study is length of hospital stay within 30 days after admission including readmissions during this period (corresponding to Module 1). Length of hospital stay will be verified based on hospital data for the index hospital stay and complemented by 30-day interviews regarding possible secondary hospitalizations.

Secondary endpoints (corresponding to Module 1–3) include measures of patient-oriented outcomes:in-hospital and all-cause 30-day mortalityunplanned readmissions or unplanned general practitioner / ED visitsdelaying factors of ED- and medical ward’s floweffective time to hospital discharge after involving external institutions (time from transfer application to transfer)institutionalizationsatisfaction with ED-, ward-, and discharge processfunctional status (incl. Quality of life) using the EuroQol Group 5-Dimension Self-Report Questionnaire (see Additional file 1) [23].

To study hospital internal processes and effects of interprofessionality, we will look at compliance and agreement of the three health professions (physicians, nursing, and social workers) in the use of “In-HospiTOOL”, and delays from the anticipated to the effective discharge date as compared to discharge date anticipated by the different health care professionals on admission and during the course of the hospital stay. We will use the above-mentioned outcome data set as benchmark to establish a risk-adjusted resource and quality cockpit to compare different hospitals and demographics (corresponding to Module 3).

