#### Difference in differences

To quantify an overall effect on length of hospital stay after implementing the “In-HospiTOOL”, we fit a patient-level multivariate linear regression model. It will include lengths of hospital stay of “control” hospitals, all risk adjusters listed above in the manuscript, and a time variable for study weeks. The dependent variable will be length of hospital stay (days in hospital). We will test for interaction between the intervention period and the intervention population and will assess whether there is a difference in the change (slope) in length of hospital stay over time between the two study populations. The intervention and control groups will have different baseline characteristics, however both groups will be exposed to similar alterations in outcomes over time without the interventional program.

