#### Interrupted time series (ITS) model

We will analyze the trends in length of hospital stay from start of observation through the end of the intervention period (18 months). For this purpose, we will conduct an ITS as a sensitivity analysis. We will implement the ITS using generalized estimating equations (GEE), to examine linear trends in weekly, hospital-level, risk-adjusted length of hospital stays. ITS models will be tested for autocorrelation to control for seasonal trends using the Durbin-Watson statistics [25]. We will analyze the change in trend between all three time periods. This approach allows us to distinguish between a possible effect of the intervention and a difference from underlying trends facing both study groups and can also help to analyse whether the intervention effects will sustain over time. We will calculate weekly-adjusted length of hospital stay using linear GEE that includes all lengths of hospital stay from the control and intervention populations and all above mentioned risk factors. We will graph weekly length of hospital stay for all populations over time and use the estimated weekly means for control and intervention patients to assess for a weekly difference between the two groups. Finally, we explore whether the adjusted weekly length of hospital stay decreases in the intervention period and whether there will be an independent time trend effect induced by the intervention only [26].

To summarize, we will use four statistically hypothesis tests during each period: (i) Are there significant trends in length of hospital stay change during the period. (ii) Will the trend differ between the control and intervention populations (the interaction between time and control or intervention conditions) during the period. (iii) Will the trend during the intervention period differ from the trend during the observation period within all three conditions. (iiii) Will the magnitude of the altered trend between the intervention and the observation period differ between the three conditions (the interaction between the change in slope and intervention or control conditions). These models will also be implemented for the analyses of the secondary endpoints.

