Our study has several potential limitations. First, inclusion of about 35`000 patients over the 18-month study time frame is ambitious. However, based on our large experience from previous multicenter studies, a well-established multicenter research network, and the high prevalence of hospitalized multimorbid patients eligible for this trial, we are convinced that the trial is feasible. The second limitation of this trial is the lack of randomization. Methodologically, in a trial whose intervention focuses on the process of care, neither patient-level randomization nor a randomized cross-over design was feasible as a carry-over effect would have biased the control group. For a cluster randomized trial, a large number of similar clusters (i.e. hospitals) would be needed – which is challenging in Switzerland particularly in light of the limited study budget. Therefore, we chose an ITS model in a quasi-experimental study design using administrative data from non-participating hospitals as a control group. Doing so, we account for differences in the patient population that may occur due to epidemiological variations. Third, as a pragmatic trial with a bundled intervention, it will be challenging to understand which part of our intervention shows clinical effects, leading to potential participation bias. Nonetheless, the large amount of health care data collected will also allow to provide scientific evidence as to which elements of patient management are influenced by the intervention.

In conclusion, this pragmatic comparative effectiveness health services research trial will inform whether the implementation of a novel electronic tool for inpatient management optimizes inter-professional collaboration and thereby reduces length of hospital stay without derogating subjective and objective patient-oriented measures. Our trial will help to compare between diverse transition processes within seven different hospitals and to create a benchmarking for inpatient care quality. This study synergizes national networks and, thus, has the potential to become a cornerstone in the present public healthcare discussion.

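### The no-harm claim for patient outcomes is paired only with tests of difference and trend, which can detect harm but cannot establish its absence

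*Protocol article*

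**What the plan says.** The no-harm statement appears as hypothesis and as intended conclusion.

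- **Module 1 (hypothesis):** the tool "will significantly shorten length of hospital stay without compromising patient outcomes and functional independence".
- **Module 2 (hypothesis, satisfaction only):** "We will systematically examine patient satisfaction, hypothesizing that it will not decrease upon the study intervention".
- **Abstract, Methods:** the trial will show whether the tool "reduces length of hospital stay without harming subjective and objective patient-oriented outcome markers".
- **Closing paragraph of the Discussion:** the trial will show whether it "reduces length of hospital stay without derogating subjective and objective patient-oriented measures".

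Under Endpoints, the single primary endpoint is days in hospital within 30 days of admission, readmissions included. The secondary endpoints "include measures of patient-oriented outcomes", among them in-hospital and 30-day mortality, unplanned readmissions or visits, institutionalisation, satisfaction and functional status by EQ-5D.

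The section on statistical analysis and sample size says that all endpoints will be compared between the three phases with covariate adjustment. The difference-in-differences model tests a group-by-period interaction and "will assess whether there is a difference in the change (slope) in length of hospital stay over time between the two study populations". The interrupted time series section lists four tests, each asking whether a trend is present or differs. It then adds: "These models will also be implemented for the analyses of the secondary endpoints".

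**The concern.** A claim that outcomes are not made worse needs evidence that rules out a harm large enough to matter. A test of difference has no harm as its null hypothesis. Rejecting that null can show harm. Failing to reject it shows only that the data did not separate the effect from zero, and this happens more often the less precise the data are. With seven hospitals, precision for a hospital-level intervention may be much lower than 35,000 patients suggest.

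The article thus states a claim and names analyses that cannot support it. At stake is the second part of the announced conclusion: shorter stay at no cost to patients could be stated while the data remain compatible with a relevant rise in deaths or readmissions.

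The primary endpoint adds a reason for care. It counts hospital days within 30 days, so a patient who dies early contributes fewer days. Excess early mortality would push the primary result in the favourable direction.

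**Working it through.** **Claim against test.** The claim is that outcomes are not compromised and that satisfaction does not fall. The stated tests are: endpoints compared between phases; interaction or difference in slope; presence of, or difference in, trends; the same models for the secondary endpoints. No non-inferiority or equivalence hypothesis, margin or confidence-limit rule is stated, and no result is named that would count as not compromised.

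**The plan's own figure.** The article gives no power calculation to reproduce. Its 35,000 is an accrual estimate: 7 sites × 2,500 to 8,000 patients per year × 1.5 years = 26,250 to 84,000, which contains 35,000. Adequate power is asserted without alpha, effect size, event rate or margin.

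**Illustration.**

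Inputs from the article: about 35,000 patients, three phases of equal length, 7 hospitals. With even accrual, n = 35,000 / 3 = 11,667 per phase.

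Assumed, because the article gives no values: 30-day mortality p of 5% or 8%; a true relative rise of 10%, so d = 0.1p; two-sided alpha 0.05; hospital-by-phase standard deviation s from 0 to 1 percentage point. The comparison is observation against intervention phase, unadjusted. For the control population the article names only length of stay as outcome data, so a before-after contrast may be all that is available for mortality.

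Formulas:
- SE = √[ 2p(1 − p)/n + 2s²/7 ]
- P(non-significant) = Φ(1.96 − d/SE), the opposite tail being negligible

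Worked case, p = 0.08, s = 0: SE = √(0.1472 / 11,667) = 0.00355. d/SE = 0.008 / 0.00355 = 2.25. Φ(1.96 − 2.25) = 0.385.

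Same p, s = 0.005: the added term is 2 × 0.000025 / 7 = 0.00000714, so SE = 0.00444, d/SE = 1.80 and Φ(0.16) = 0.564.

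| p | d (points) | s (points) | 95% half-width (points) | P(non-significant) |
|---|---|---|---|---|
| 5% | 0.5 | 0 | 0.56 | 0.58 |
| 5% | 0.5 | 0.25 | 0.62 | 0.65 |
| 5% | 0.5 | 0.5 | 0.77 | 0.75 |
| 5% | 0.5 | 1.0 | 1.19 | 0.87 |
| 8% | 0.8 | 0 | 0.70 | 0.39 |
| 8% | 0.8 | 0.25 | 0.74 | 0.44 |
| 8% | 0.8 | 0.5 | 0.87 | 0.56 |
| 8% | 0.8 | 1.0 | 1.26 | 0.76 |

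**Limit of the illustration.** With independent patients, power to detect a 1-point rise is 92% at a 5% event rate, 70% at 10% and 47% at 20%. At the lower rates a harm of a full point or more would usually be seen. The gap concerns small to moderate absolute harms, and it widens with clustering: at an assumed design effect of 5, the same three powers fall to 32%, 20% and 13%.

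**The case against.** The strongest reply is that this is a condensed article and its analysis plan is not shown. Margins and interval rules for secondary endpoints are commonly left to that plan, and a difference-in-differences or GEE model yields the estimate and interval that a non-inferiority rule needs. That stands in part: the absence of margin values is not the point, and nothing in the article excludes a later margin. But the article goes further than silence. It names the tests, says the same models serve the secondary endpoints, and pairs them with a claim those tests cannot carry. That mismatch is on the page.

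A reader might infer that a non-significant harm will be reported as safety. The documents do not support this: no section gives such a rule. What can be said is that no other criterion is offered.

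A reader might also treat absence of harm as co-equal with shorter stay. It is not: length of stay is the sole primary endpoint. The article elsewhere expects outcomes and satisfaction to improve, an aim for which tests of difference are suitable. The hypothesis of no decrease is stated for satisfaction only.

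Two protections deserve credit. Readmission days count in the primary endpoint, so premature discharge followed by return counts against the tool. Deaths are recorded as separate endpoints.

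Finally, the illustration is not the planned analysis, which is adjusted and uses interactions and weekly trends, and its rates and hospital variation are assumed. This stands, so the figures indicate scale only.

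**Conclusion.** The concern holds as a mismatch between a stated claim and the stated tests. As written, the article contains no analysis that could support the no-harm part of its hypothesis and conclusion.

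For a true 10% relative rise in 30-day mortality, the chance of a non-significant result is about 39% at 8% mortality and 58% at 5% with independent patients. It is 56% and 75% if the hospital-by-phase standard deviation is 0.5 points. These figures rest on even accrual, assumed mortality and hospital variation, and a simple two-phase comparison. They show that small to moderate harms could go undetected, not that large ones would.

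The analysis of the primary endpoint is not invalidated. The point should be settled before analysis because it governs a headline conclusion.

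**What to change.** 1. Before analysis, set non-inferiority margins, justified by the sponsor, for 30-day mortality, unplanned readmission, EQ-5D and satisfaction.
2. State that absence of harm is claimed for an outcome only if the harm-side confidence limit, allowing for clustering by hospital, lies inside its margin. Otherwise give the estimate and interval and state that absence of harm was not shown.
3. If no margins can be agreed, drop the no-harm wording and report estimates with intervals.
4. Report days alive and out of hospital to day 30 as a supportive analysis. Hospital days and deaths over this window are already to be collected; the calculation also assumes that dates of death are available.

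**Cost.** No new patients are needed, only wording in the analysis plan and agreement on margins. The downside is that the no-harm claim becomes harder to make. To show the scale, without proposing values: with one-sided alpha 0.025, 80% power, no true difference and independent patients, n per phase = (1.96 + 0.84)² × 2p(1 − p) / margin². At 5% mortality this gives 29,826, 7,457 and 1,865 for margins of 0.5, 1 and 2 points; at 8%, 46,215, 11,554 and 2,889. Against about 11,667 per phase, a 0.5-point margin is out of reach, a 1-point margin is just attainable at 8%, and a 2-point margin is comfortable. Clustering raises all of these.
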